# Aspirin for metal stent in malignant distal common bile duct obstruction (AIMS): study protocol for a multicenter randomized controlled trial

**DOI:** 10.1186/s13063-020-4083-z

**Published:** 2020-01-30

**Keywords:** Endoscopic retrograde cholangiopancreatography, Self-expandable metallic stents, Randomized controlled trial, Aspirin

## Abstract

**Background:**

Endoscopic retrograde biliary drainage (ERBD) is the treatment of choice for patients with malignant distal common bile duct (CBD) obstruction. Self-expandable metal stents (SEMS), which are commonly used in unresectable cases, have many clinical advantages, including longer stent patency. Although the expected patency of SEMS is around 8 months, it has recently been reported that the duration of SEMS’ patency in patients using aspirin is prolonged. Our study, therefore, aims to investigate the effect of aspirin on SEMS’ patency.

**Methods/design:**

This is an investigator-initiated, prospective, multicenter, double-blind, randomized placebo-controlled trial that will be conducted from November 2017 in four tertiary centers in South Korea. We intend to include in our study 184 adult (aged ≥ 20 years) patients with malignant distal CBD obstruction for whom ERBD with SEMS was successfully performed. The patients will be randomly allocated to two groups, which will comprise patients who have either taken 100 mg aspirin or a placebo for 6 months after index ERBD. The primary outcome will be the rate of stent dysfunction, and the secondary outcomes will be the duration of patency, the rate of reintervention, and the occurrence of adverse events.

**Discussion:**

The aspirin for metal stents in malignant distal common bile duct obstruction (AIMS) study should determine the efficacy of aspirin in maintaining metal-stent patency in patients with malignant distal CBD obstructive.

**Trial registration:**

ClinicalTrials.gov, ID: NCT03279809. Registered on 5 September 2017.

## Background

Endoscopic biliary drainage for malignant distal common bile duct (CBD) obstruction is the modality of choice that could resolve multiple clinical problems for patients with conditions such as jaundice, pain, sepsis, and organ failure. Several studies, including a meta-analysis, have reported that self-expandable metal stents (SEMS) have advantages over plastic stents in terms of stent patency, adverse events, revisions, and the survival of patients with malignant biliary obstruction [1–7]. It is important to maintain stent patency because cholangitis may occur due to stent dysfunction, which may affect patients’ prognoses.

SEMS do not maintain patency for long periods within an overall life span because the stent may become obstructed due to, predominantly, tumor ingrowth or overgrowth, sludge deposition, biofilm formation, or epithelial hyperplasia [8–10]. Some of these factors may be affected by aspirin when considering the pharmacological mechanisms of aspirin. Aspirin affects the cyclooxygenase pathway and prostaglandin production, which suggests that it has the potential to reduce mucin secretion and inhibit gallstone formation [11]. However, the use of systemic drugs, including ursodeoxycholic acid (UDCA) and antibiotics, to effectively prevent stent dysfunction, has not been reported [12].

Lee et al. found experimental evidence supporting the inhibitory effect of aspirin on glycoprotein secretion and crystal and stone formation in dogs [13]. It has also been reported that aspirin decreases the viscosity of bile [14, 15]. A study by Rhodes et al. found that treating patients with aspirin reduced the production of mucin in the gallbladder compared with those not treated with aspirin [16], while Sterling et al. found that the concentration of gallbladder mucin was significantly lower in chronic non-steroidal anti-inflammatory drug users [17]. However, the results of these studies regarding the true effects of aspirin were unclear. Paul et al. reported that UDCA had a marked effect on inhibiting gallstone formation, but aspirin had no significant effect [18]. Sahlin et al. advocated that the degree of stone formation does not change according to the protein content of bile and presumed that only UDCA changes the constitution of bile because the protein composition of bile was only different in the group treated with UDCA in their study, as in the case of aspirin and chenodeoxycholic acid [19].

The results of a recent large retrospective cohort study conducted by Jang et al. showed that SEMS’ occlusion in malignant distal CBD obstruction was significantly less likely among patients taking aspirin [11]. Importantly, their study suggested that the use of systemic drugs can improve stent patency. This is contrary to previous studies that have mostly focused on the type, shape, and functional aspects of stents. In this study, we aim to determine whether aspirin use has a positive effect on the patency of SEMS in unresectable, malignant, distal CBD obstruction.

## Methods/design

Our study on aspirin for metal stents in malignant distal common bile duct obstruction (AIMS) is an investigator-initiated, randomized, multicenter, double-blinded, placebo-controlled, prospective comparative study. We will perform the study in accordance with the common guidelines for clinical trials in accordance with the Declaration of Helsinki and International Conference on Harmonization and World Health Organization Good Clinical Practice (ICH-GCP) standards. This study protocol was approved by the Institutional Review Board of Seoul National University Hospital, South Korea (IRB No. H-1707-161-874). This trial was registered with ClinicalTrials.gov (ID: NCT03279809) on 5 September 2017. Figure 1 shows the overall scheme for the AIMS study and Fig. 2 the Standard Protocol Items: Recommendations for Interventional Trials (SPIRIT) Figure and Additional file 1 the SPIRIT Checklist.

**Fig. 1 Fig1:**
[figure not shown]
Overall scheme of the aspirin for metal stents in malignant distal common bile duct obstruction (AIMS) study

**Fig. 2 Fig2:**
[figure not shown]
Schedule of enrollment and assessments

### Population

Patients who need endoscopic biliary drainage for malignant distal CBD obstruction, and who have been referred to tertiary centers, will be recruited for the trial. The target sample size is 184 subjects in the tertiary referral centers in South Korea (i.e., Seoul National University Hospital, Wonju Severance Christian Hospital, Myongji Hospital, and Yongin Severance Hospital). Our study will be informed to patients who are considered eligible for the trial. All the eligible candidates will undergo an interview and receive more detailed information regarding the study, the intervention, and the two ways to manage index SEMS’ placement for malignant distal CBD obstruction. The candidates will then receive either aspirin or a placebo in a double-blind manner since evidence on the effect of aspirin for SEMS’ maintenance is unclear. The participants’ written informed consent will be obtained and archived securely in document form. The participants will be provided with comprehensive information regarding the study aim, intervention, and potential risks and benefits, and will be able to withdraw from the study at any time without consequence. The trial will commence from November 2017 and conclude 6 months after the last patient enrollment. All the recruitment procedures will be recorded in a log file.

### Inclusion criteria

The participants meeting the following criteria will be included:
Aged 20 years or olderHave unresectable, malignant distal CBD obstructionTechnically successful placement of the index ERBD with a SEMS

### Exclusion criteria

Participants meeting one or more of the following criteria will be excluded from the study:
Patient refusalPatient underwent previous SEMS’ placementCurrent aspirin userHistory of allergic reaction to aspirinContraindication to aspirinLife expectancy less than 6 monthsActive peptic ulcer or gastrointestinal bleedingHistory of drug (substance) abuseRegistration for other clinical trials within 30 days

### Randomization, blinding, and treatment allocation

The randomization lists will be generated using Random Allocation Software version 1.0.0 (free software developed by M. Saghaei, MD, Isfahan University of Medical Science, Isfahan, Iran) using the block randomization method developed by a research fellow at Seoul National University Hospital who is not involved in our trial. The patients who meet the selection criteria will be randomized at a 1:1 ratio in each group (test or control). As this is a double-blinded study, the researchers, patients, and other study personnel will be blinded to the treatment.

### Interventions and management of the study drug

The enrolled patients will be randomly assigned to the test group or the control group. The drug administration will start within 30 days of successful placement of the index ERBD with a SEMS. The specifications of the stent (covered/partially covered/uncovered, caliber, length) were also decided by the physician’s discretion, taking into account the feature of obstruction site and the patient’s condition. And we allow the use of all biliary SEMS available in each institution regardless of manufacturers including the WallFlex biliary stent (Boston Scientific, Natick, MA, USA), the Bonastent (Standard SciTech Inc., Seoul, South Korea), the Niti-S biliary stent (Taewoong Medical Co., Ltd., Ilsan, South Korea), the Zilver biliary self-expanding stent (Wilson-Cook Medical Inc., Winston Salem, NC, USA), and the ARISTENT (CGbio Co., Ltd., Seongnam-si, South Korea), etc. Prophylactic rectally administered indomethacin or rectally administered diclofenac for post-procedural pancreatitis will not be used because none of the rectally administered non-steroidal anti-inflammatory drugs is commercially available in Korea. The patients in the test group will take one 100-mg enteric-coated aspirin tablet (Daewon Pharmaceutical Co., Ltd., Seoul, South Korea) per day before or after meals for 6 months, which was known to be physiologically equivalent to 75 mg plain aspirin [20]. And the patients in the control group will take one placebo tablet for 6 months. We planned a longer period of aspirin use for 6 months in comparison with the previous retrospective study [11] because the known median patency of SEMS in distal CBD obstruction was over 6 months [1, 5]. The patients will be followed-up in an outpatient clinic irrespective of whether the clinical outcomes, including stent malfunction, occur. Anti-cancer therapy, which is or will be received, will continue regardless of whether the patient is enrolled in the study.

The initial drug distribution and storage will be handled by the clinical trials center pharmacy of Seoul National University Hospital. Thirty-five tablets will be packaged in each medicine bottle, which will have a random number on the front label. After screening and enrollment, a randomization number will be assigned to each patient, and a prescribed number of medications will be given to them based on the randomization number. Each patient will be prescribed one bottle every 4 weeks according to the follow-up schedule, and the number of drugs remaining at the following outpatient visit will be retrieved to assess patient compliance. A research nurse will conduct frequent telephone monitoring to be prepared for the cases that lose or do not return the drug bottle.

During the follow-up period, the study patients will be instructed not to take medicines that are prohibited in conjunction with aspirin according to the pharmaceutical authorization from the Korean Ministry of Food and Drug Safety. When taking new medicines during the study period, the patients will be required to contact the researchers so that they can evaluate the drugs’ interactions with aspirin and effect on the research sustainability. The detailed principles of the concomitant use of drugs in this study are as follows:
Anticoagulants, thrombolytics, other platelet-aggregation inhibitors, hemostatic agents: de-escalation of dose or careful administrationOther non-steroidal anti-inflammatory drugs and salicylic acid preparations: discontinue administration if possible, do not concomitant use due to increased risk of bleeding or decreased renal functionHigh-dose methotrexate over 15 mg/week: do not use due to increment of toxicityLithium: careful administration due to the possibility of lithium poisoningSelective serotonin-reuptake inhibitors: careful administration due to increased risk of upper gastrointestinal bleedingDigoxin: careful administration due to increment of plasma digoxin levelValproic acid: careful administration due to increment of toxicityAlcohol: careful use due to increment of gastrointestinal mucosal damage, prolonged bleeding time

### Study outcome and assessment

The primary outcome of this study is the rate of stent dysfunction at 6 months. Stent dysfunction is defined as the presence of symptoms of obstructive jaundice or cholangitis in combination with confirmation of stent obstruction or migration via imaging (i.e., computed tomography and/or magnetic resonance imaging) after index SEMS’ insertion. Cholangitis will be diagnosed according to the Tokyo Guideline 2013 as follows: fever over 38 °C, evidence of an inflammatory response with an abnormal white blood cell level (< 4000/uL or > 10,000/uL) or a C-reactive protein level ≥ 1 mg/dL, jaundice (total bilirubin ≥2 mg/dL), abnormal liver function tests (alkaline phosphatase, gamma-glutamyl transferase, alanine transaminase, aspartate transaminase > 1.5 x standard deviation), and biliary dilatation at imaging tests [21]. The rate of stent dysfunction is defined as the percentage of patients who develop stent dysfunction during the follow-up period.

The secondary outcomes of this study are the duration of stent patency, the rate of reintervention, and any adverse events related to aspirin administration. The duration of stent patency will be evaluated on a day-scale as the duration between the index SEMS’ placement and the occurrence of stent dysfunction, or death in the case of patients without stent dysfunction. The rate of reintervention is defined as the percentage of patients who underwent an additional intervention for biliary drainage during the follow-up period after the index SEMS’ placement. For adverse events, a thorough investigation will be conducted to determine whether the adverse effects were related to aspirin administration.

Baseline characteristics and medical information of patients are also recorded in detail through the case report form including information as follows for further analysis: etiology, stage of disease, histologic feature, Charlson’s comorbidity index, history of hypertension, diabetes mellitus, pulmonary tuberculosis, cerebrovascular disease, coronary artery disease, liver or bile duct disease, peptic ulcer disease, any bleeding event, drugs in current use, smoking, alcohol use, family history, prior management including sphincterotomy, whether any biliary stent, further management including detailed information of chemotherapy, radiotherapy, surgery.

The patients will visit the outpatient clinic at 4, 12, and 24 weeks after index ERBD where their clinical symptoms will be evaluated and laboratory tests conducted to assess their vital signs, the presence of Charcot’s triad (jaundice, fever, and right upper quadrant abdominal pain), white blood cell count, hemoglobin, platelets, blood urea nitrogen, creatinine, total bilirubin, alkaline phosphatase, alanine transaminase, aspartate transaminase, C-reactive protein, prothrombin time, and the results of imaging tests such as computed tomography, magnetic resonance imaging, or endoscopic ultrasonography. Additional visits to the outpatient clinic or emergency room at the follow-up center will be allowed if worrisome symptoms or signs become apparent.

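### The primary-endpoint definition accepts only CT or MRI as proof of stent failure and prints a liver-test limit that cannot be applied

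*Protocol article*

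**What the plan says.** All of the defining text is in the protocol article, Methods/design, Study outcome and assessment.

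- Endpoint: "The primary outcome of this study is the rate of stent dysfunction at 6 months".
- Event: "the presence of symptoms of obstructive jaundice or cholangitis in combination with confirmation of stent obstruction or migration", where the confirmation is "confirmation of stent obstruction or migration via imaging (i.e., computed tomography and/or magnetic resonance imaging").
- Cholangitis: "Cholangitis will be diagnosed according to the Tokyo Guideline 2013 as follows". Five items follow: fever, inflammatory response, jaundice (total bilirubin of at least 2 mg/dL), abnormal liver tests and biliary dilatation. The list closes with "alanine transaminase, aspartate transaminase > 1.5 x standard deviation), and biliary dilatation at imaging tests".
- Reintervention, a separate secondary outcome: the "percentage of patients who underwent an additional intervention for biliary drainage during the follow-up period".
- Duration of patency, also secondary: from index placement to dysfunction or, for patients without dysfunction, to death.

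**The concern.** This is the trial's only primary endpoint, and two parts of its definition do not work as printed.

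First, a stent can be shown to have failed without CT or MRI, for example when a symptomatic patient goes to endoscopic reintervention and the occluded or displaced stent is seen there. The printed wording leaves that patient out of the primary event count. The same patient's patency time could then run on to death, so the secondary time-to-event outcome is affected too.

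Second, a liver-test limit of 1.5 times a standard deviation has no mean, reference limit or standard deviation attached. Whoever classifies the event must supply a limit that the article does not state.

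A lesser point is that the five cholangitis items are joined by and, with no statement of how many must be present.

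The stake is lost events. Missing the same share in both arms lowers both rates and shrinks the absolute difference, which costs power.

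**Working it through.** **1. How the wording classifies a patient.** Take a patient with obstructive jaundice or cholangitis, no CT or MRI, and a blocked stent seen at reintervention.

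| Outcome | Condition in the text | Result |
|---|---|---|
| Stent dysfunction (primary) | symptoms and CT/MRI confirmation | not met |
| Reintervention (secondary) | additional biliary drainage | met |
| Duration of patency (secondary) | ends at dysfunction, otherwise at death | could run to death |

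Nothing elsewhere in the article adds another route to confirmation.

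**2. The cholangitis list.** Suppose all five items were required. Bilirubin of at least 2 mg/dL would then be necessary, so every patient with cholangitis would already be jaundiced. The cholangitis branch of the event definition would add almost no one to the jaundice branch, although the sentence offers the two as alternatives. If the guideline's own combination rule is meant, this problem disappears, but the text does not say so.

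**3. The plan's own sample size.** Inputs from Sample size: control rate 40%, two-sided 5% level, 80% power, 10% dropout. The 1:1 allocation is from Randomization, blinding, and treatment allocation. The sentence giving 20% is garbled. I take 20% as the aspirin-arm rate, which is close to 0.49 × 40% = 19.6%.

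Pooled-variance formula, with p̄ = 0.30:

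n = [1.960 × √(2 × 0.30 × 0.70) + 0.842 × √(0.24 + 0.16)]² / 0.20²

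= [1.270 + 0.532]² / 0.04 ≈ 81.2, so 82 per arm.

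Dropout: 82 / 0.90 = 91.1, so 92 per arm and 184 in total. The stated figures reproduce.

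**4. Power if failures are missed.** Let s be the share of true failures that the definition captures, equal in both arms, with no false positives. The article gives no value for s, so the range below is assumed. With p1 = 0.40s, p2 = 0.20s and p̄ their mean:

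Power = Φ{ [(p1 − p2)√82 − 1.960 × √(2p̄(1 − p̄))] / √(p1(1 − p1) + p2(1 − p2)) }

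For s = 1: (1.811 − 1.270) / 0.632 = 0.855, so power is 80.4%.

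For s = 0.8: (1.449 − 1.184) / 0.593 = 0.447, so power is 67.2%.

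| s | Rates | Power at 82 per arm | n per arm for 80% | Total with 10% dropout |
|---|---|---|---|---|
| 1.0 | 40% v 20% | 80.4% | 82 | 184 |
| 0.9 | 36% v 18% | 74.2% | 95 | 212 |
| 0.8 | 32% v 16% | 67.2% | 111 | 248 |
| 0.7 | 28% v 14% | 59.7% | 132 | 294 |

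The design has almost no reserve: 80.4% against a target of 80%.

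**The case against.** **Cross-sectional imaging may be a deliberate choice of objective proof.** That is possible. The article does not say that patients go to reintervention without CT or MRI, or how often. Reinterventions are also counted separately, so these patients are not invisible. This limits what can be said about size. It does not change how such a patient is classified.

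**The guideline supplies the cholangitis rule.** A reader might infer that all five items are required and that cholangitis without jaundice is lost. The article does not establish this. It names a published guideline, never says all of, and condenses a fuller protocol that is not shown. The point also touches only patients who do not already qualify through obstructive jaundice. What stands is a request for one clarifying sentence.

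**The visit schedule does not contradict the endpoint.** The follow-up paragraph lists "the results of imaging tests such as computed tomography, magnetic resonance imaging, or endoscopic ultrasonography". Collecting more imaging than the endpoint uses is consistent. Nor is anything wrong because gamma-glutamyl transferase is a criterion but not a scheduled test: extra visits are allowed and their tests are not restricted.

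**Centres may not differ.** A reader might expect the four centres to differ in imaging or reintervention habits. The article gives no evidence of that.

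**The power loss is hypothetical.** This stands. The 40% comes from other studies' reported occlusion rates, whose definitions are not shown and which may already reflect imperfect detection. The endpoint also counts migration, which pushes the observed rate up. The net effect is unknown.

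**The standard-deviation cut has no known direction.** This also stands. It is unworkable rather than shown to lose events, and it is one part of one item in one of two symptom branches.

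**Conclusion.** Two defects hold on the face of the text. Confirmation is closed to CT and/or MRI, so a symptomatic failure shown only by direct endoscopic or cholangiographic finding is scored as no dysfunction. The liver-test limit has no reference value and cannot be applied. The missing combination rule for cholangitis is a matter for clarification.

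The size of any misclassification cannot be derived from the article. The fall in power from 80% to 74%, 67% or 60% assumes that 10%, 20% or 30% of true failures are missed equally in both arms, that there are no false positives, and that 40% v 20% are the full-capture rates.

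A reader might go further and infer bias towards one arm or a faulty sample size. Neither is supported. The trial is double-blind and the article gives no reason for unequal loss, and the sample size reproduces from its own inputs. The point should be corrected, but it does not invalidate the design.

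**What to change.** Before unblinding, and identically for all centres:

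1. Count obstruction or migration in a symptomatic patient when confirmed by CT, MRI, endoscopic ultrasonography, or a direct endoscopic or cholangiographic finding at a reintervention done for clinical reasons.
2. Keep CT/MRI-only confirmation as a sensitivity analysis, so that the effect of the wider definition is visible.
3. Replace the standard-deviation cut with a multiple of a defined laboratory reference limit, taken from the cited guideline.
4. State that the cited guideline's own combination rule decides which items make cholangitis.
5. Use the same event classification for duration of patency.

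Cost: the rewording is short and calls for no new procedures on patients. It does change the primary endpoint of a registered trial, so it needs an Institutional Review Board modification and communication to study personnel, as the section Protocol modifications requires. The case report form items listed in the article do not mention findings at reintervention. The sponsor should check that these are captured and, if not, retrieve them from source records.

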### Sample size

We calculated the sample size for this study based on the results of a previous retrospective study with a similar clinical situation and purpose [11]. In the study, stent occlusion occurred in 15.3% of the patients in the aspirin group and 23.4% of the patients in the non-aspirin group at a mean of 3 months during the follow-up period. Based on the findings of other studies, we assumed a 40% stent occlusion rate of SEMS in malignant distal CBD obstruction after 6 months [9, 25–27]. Furthermore, we assumed the rate of stent dysfunction on the basis of a recent study that reported the hazard ratio (0.49; 95% confidence interval, 0.32–0.75) was lower in the patients in the aspirin-test group as opposed to 20% in the non-aspirin group [11]. Our calculations were performed using 80% power and a two-sided 5% significance level to verify the null hypothesis and the alternative hypothesis. The sample size required to demonstrate this was calculated as 82 patients in each group and 184 patients in the total sample (92 patients per 10% dropout rate).

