### Data analysis

Blinding will remain in place until the statistician codes the statistical analyses of the primary and secondary outcomes. The statistical analyses will be done using the full analysis set according to the intention-to-treat principle, meaning that all the randomized patients will be analyzed in their allocated groups regardless of any protocol violations or early treatment discontinuations. We will also evaluate the outcomes through a per-protocol analysis set that will consider only the subjects who followed the protocol effectively. No formal interim analysis is planned.

We will compare the rate of stent dysfunction using Pearson’s chi-squared test with Fisher’s exact test and calculate the odds ratio of the event. The secondary outcomes (i.e., the duration of stent patency, the rate of reintervention, and the adverse events related to aspirin administration) will be analyzed using Pearson’s chi-squared test with Fisher’s exact test, Student’s *t* test and Kaplan-Meier curves, stratified by drug, and the hazard ratios between two groups measured using the Cox proportional hazards regression. We also plan to identify the further affecting factors for stent dysfunction by univariate and multivariate logistic regression analysis.

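### Duration of stent patency (secondary outcome) ends at death, has no value for patients alive without dysfunction, and has a t test listed beside Kaplan-Meier and Cox

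*Protocol article*

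**What the plan says.** Study outcome and assessment (protocol article) measures the duration of stent patency in days from placement of the index stent to "the occurrence of stent dysfunction, or death in the case of patients without stent dysfunction". It names no end date for a patient who is alive without dysfunction when follow-up stops. It also does not say whether death is an event or a censoring.

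Data analysis names the methods for the three secondary outcomes as one group. After the chi-squared and Fisher tests come "Student’s *t* test and Kaplan-Meier curves, stratified by drug", and then "the hazard ratios between two groups measured using the Cox proportional hazards regression". No method is assigned to a particular outcome, and none is named as leading.

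Two other statements show how many durations will be incomplete. Interventions and management of the study drug says that "the known median patency of SEMS in distal CBD obstruction was over 6 months". Sample size says "we assumed a 40% stent occlusion rate of SEMS in malignant distal CBD obstruction after 6 months". The scheduled visits end at 24 weeks.

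**The concern.** The other two secondary outcomes, reintervention and adverse events, are rates or events, so the t test can only sensibly be meant for patency duration. That duration is heavily censored. On the plan's own figures, well over half of the patients have no dysfunction at 6 months, and those who are also alive then have no defined value.

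A t test can handle this in two ways, and neither is valid:

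- It can use only the patients who had dysfunction or died. This selects on the outcome and discards the patients in whom the stent lasted longest.
- It can treat the cut-off date as if it were the duration. This understates the longest patencies.

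The definition also matters for the survival methods. If Kaplan-Meier and Cox take over the stated end point, a patient who dies with a working stent counts as a patency failure. The result then describes dysfunction or death, not patency.

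Longer patency is the trial's rationale, and this is the only outcome that measures it directly as a duration. With several methods listed and none leading, a near-null t test and a Cox hazard ratio could be reported from the same data with no rule for choosing between them.

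**Working it through.** **Inputs from the documents.** Sample size gives 40% control dysfunction at 6 months, a "hazard ratio (0.49; 95% confidence interval, 0.32–0.75", 80% power, a two-sided 5% level, 82 per group, and 92 per group after 10% dropout.

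**Assumptions not in the documents.** Constant hazards; deaths without dysfunction independent of dysfunction and equal in both arms, 10%, 20% or 30% by 6 months; 6 months' follow-up for everyone.

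**The plan's own figure.** For 40% v 20%, pooled variance, no continuity correction:

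n = [1.96·√(2·0.3·0.7) + 0.8416·√(0.4·0.6 + 0.2·0.8)]² / 0.2² = (1.270 + 0.532)² / 0.04 ≈ 81.2, so 82 per group. Then 82/0.9 = 91.1, so 92 per group and 184 in all. The stated size is reproduced. (The text attaches 20% to the non-aspirin group, but 40% v 20% is the pair that gives 82.) No power is stated for patency duration, so there is no figure for it to reproduce.

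**Hazards and the share without dysfunction.**
- Control: λ₀ = −ln(0.6)/6 = 0.0851 per month.
- Aspirin: λ₁ = 0.49 × 0.0851 = 0.0417 per month.
- Dysfunction on aspirin at 6 months: 1 − 0.6^0.49 = 22.1%.
- So 60% of control and 78% of aspirin patients have no dysfunction at 6 months, leaving deaths aside.
- True medians, ln 2/λ: 8.1 v 16.6 months.

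**What a t test on observed dysfunction times sees.** Mean time among patients with dysfunction by 6 months = 1/λ − 6·S(6)/[1 − S(6)], where S(6) = e^(−6λ):
- Control: 11.75 − 6·0.6/0.4 = 2.75 months.
- Aspirin: 23.97 − 6·0.7786/0.2214 = 2.87 months.

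The difference is about 0.13 months, or 4 days, although the true medians differ twofold.

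**Dilution if death is an event.** With death hazard δ = −ln(1 − d)/6 in both arms, the hazard ratio becomes (λ₁ + δ)/(λ₀ + δ):

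| Deaths by 6 months (assumed) | δ | Hazard ratio for dysfunction or death |
|---|---|---|
| 10% | 0.0176 | 0.0593/0.1027 = 0.58 |
| 20% | 0.0372 | 0.0789/0.1223 = 0.65 |
| 30% | 0.0594 | 0.1012/0.1446 = 0.70 |

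**Simulated power.** 92 per arm, 4,000 trials per setting, at 10/20/30% deaths:

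| Analysis | No dropout | 10% dropout |
|---|---|---|
| t test, defined durations only | 6/6/7% | 6–7% |
| t test, cut-off time used as duration | 53/44/36% | 44/36/32% |
| Log-rank, death as event | 62/51/41% | 61/49/40% |
| Log-rank, dysfunction only, death censored | 74/71/69% | 71/68/66% |

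The log-rank test stands in for Cox, since it is equivalent to the Cox score test. Without dropout, only 38–52% of patients have a defined duration over this range of deaths. Simulation error is at most √(0.5·0.5/4000), about 0.8 percentage points.

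**The case against.** The strongest reply is that the sentence listing the t test also plans Kaplan-Meier and Cox. A reader might infer that the trial as planned would miss a halving of the hazard. The documents do not support that. It is shown for the t test only. A Cox model that censors patients alive without dysfunction, and does not count death as loss of patency, keeps about two thirds to three quarters power. Nothing says that the t test decides the patency result.

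Nor do the documents state that death is an event. Ending a duration at death is compatible with censoring there. This stands as a caution, but the definition gives death the same place as dysfunction, and the two readings give different hazard ratios.

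A reader might also infer that a mean or median patency cannot be estimated at all. That assumes everyone stops at 6 months. Visits end at 24 weeks, but the trial runs until 6 months after the last enrolment, with recruitment from October 2017 to a planned September 2019, and rates are counted over an unspecified follow-up period. With an assumed 6–30 months' follow-up and 10–50% deaths by 6 months, power is 22–30% for the t test on defined durations, 35–89% with death as an event and 77–95% with death censored. The ranking of the methods is unchanged.

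Detailed censoring rules are often left to a fuller document, so their absence alone would be no point. What remains is in the stated text: a t test unsuited to censored durations, and a definition that ends patency at death.

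Finally, even the correct analysis reaches only 66–71% with 10% dropout. That part of the shortfall comes from the sample size, not from the definition.

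**Conclusion.** The point holds as a moderate one on a secondary outcome. The t test is invalid for these data: with 6 months' follow-up its power against a hazard ratio of 0.49 is about 6–7% on the durations as defined, and roughly a third to a half when cut-off times stand in for durations. Counting death as loss of patency moves the hazard ratio from 0.49 to about 0.58–0.70. With 10% dropout it lowers power to about 40–61%, against about 66–71% for dysfunction alone.

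The planned Cox analysis is sound once the event and the censoring are stated. The primary outcome is a comparison of proportions and is not affected.

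The sizes rest on constant hazards, equal and independent deaths of 10–30% by 6 months, and a 6-month horizon, none of which the documents fix. At 10% deaths the gap between the two readings of death is only about 10 points (61% v 71%). The unsuitability of the t test does not depend on the death rate.

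**What to change.** - In Data analysis, delete Student's t test for duration of patency.
- In Study outcome and assessment, define patency as time from index stent placement to stent dysfunction, and censor patients alive without dysfunction at last follow-up.
- Treat death without dysfunction as a competing event. Name the cause-specific Cox model and log-rank test, with deaths censored at the date of death, as the lead analysis. Show cumulative incidence curves that account for death, because one minus Kaplan-Meier with deaths censored overstates the proportion who will have dysfunction.
- If dysfunction or death is also of interest, report it as a labelled supportive analysis.
- Restricted mean patency time to 6 months is an optional summary in days. Under the assumptions above, leaving deaths aside, it would be 4.70 v 5.31 months.

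The cost is about two sentences. The definition already requires the dysfunction and death dates on a day scale, and follow-up visits supply the last-contact date. The change should be made before unblinding.
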